### Analysis population {27b}

All randomized participants will be included in the analysis according to the group to which they were allocated (intention-to-treat, ITT). A per-protocol analysis will also be conducted for adherence-related outcomes, where compliance is defined as use of the provided iron cookware for ≥ 1 main meal per day on ≥ 4 days per week for at least 70% of the intervention period.

### Missing data {27c}

Missing outcome data will be addressed using maximum likelihood estimation under the missing-at-random assumption. Multiple imputation with 20 datasets will be performed as a sensitivity analysis. Reasons for missingness (e.g., pregnancy, migration, withdrawal) will be documented. Additional sensitivity analyses will include complete-case analysis and per-protocol analysis to evaluate robustness of findings.

### Additional analyses {27d}

Pre-specified subgroup analyses will assess effect modification by baseline anaemia status (anaemic vs non-anaemic), dietary iron intake categories, and CRP-adjusted vs unadjusted ferritin. Mixed-effects regression models will be applied with adjustment for covariates including age, body mass index (BMI), baseline iron status, dietary intake, inflammation (CRP), and socioeconomic status. Sensitivity analyses will test the robustness of results to exclusion of participants with elevated CRP, alternative adherence thresholds, and different imputation strategies. An exploratory cost-effectiveness analysis will be conducted, estimating the incremental cost per unit increase in haemoglobin (g/dL) and ferritin (µg/L).

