### Outcomes {16}

The outcome measures and assessment time points are summarized in Table 1. Blood samples will be collected at each time point for the biochemical analysis of iron status markers. Dietary intake and adherence to cookware use will be monitored using structured questionnaires and periodic household visits.

**Table 1 Tab1:** Summary of primary, secondary, and exploratory outcomes with measurement variables, analysis metrics, aggregation methods, and time points (baseline to 12 months)

Outcome type	Measurement variable	Analysis metric	Method of aggregation	Time points
Primary outcome	Serum ferritin (µg/L), CRP-adjusted	Mean change from baseline	Mean ± SD, mean difference (95% CI)	Baseline, 6 months, 12 months
Secondary outcomes	Haemoglobin (g/dL)	Mean change from baseline	Mean difference (95% CI)	Baseline, 6 months, 12 months
	Soluble transferrin receptor (mg/L)	Mean change from baseline	Mean difference (95% CI)	Baseline, 6 months, 12 months
	Transferrin saturation (%)	Mean change from baseline	Mean difference (95% CI)	Baseline, 6 months, 12 months
	Anaemia prevalence (Hb < 12 g/dL, WHO)	Proportion with anaemia	Risk difference, risk ratio (95% CI)	Baseline, 6 months, 12 months
	Nutrition knowledge and practice score	Change in score	Mean difference	Baseline, 6 months, 12 months
	Adherence to iron cookware use (≥ 1 main meal/day, ≥ 4 days/week)	Proportion adherent	Percentage adherence	Monthly monitoring; summarised at 6 months, 12 months
	Adverse events (GI symptoms, iron overload, other harms)	Proportion with ≥ 1 adverse event	Frequency counts, percentages	Ongoing; summarised at 3, 6, and 12 months
Exploratory outcomes	Cost-effectiveness (per unit Hb and ferritin increase)	Incremental cost-effectiveness ratio (ICER)	ICER	6 months, 12 months
	Dietary modifiers (vitamin C intake, tea/coffee, phytates)	Effect modification	Subgroup analyses	Baseline, 6 months, 12 months
	Subgroup analysis by baseline anaemia	Effect difference	Interaction tests	6 months, 12 months
	Community-level adoption of cookware post-trial	Proportion of households continuing usage	Adoption rate (%)	Endline at 12 months; post-trial sustainability follow-up

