### Participant timeline {18}

#### Sample size {19}

The sample size was calculated based on hemoglobin (Hb) as the key outcome variable. Considering a standard deviation (SD) of 1.2 g/dL and a minimum detectable difference (Δ) of 0.5 g/dL between the intervention and control groups, the required sample size was estimated to provide 80% power (*β* = 0.20) at a two-sided significance level of 5% (*α* = 0.05, 95% confidence level). The sample size was adjusted accordingly to account for an anticipated 10% attrition due to loss to follow-up, pregnancy, or withdrawal. The final required sample size is 202 participants, with 101 participants allocated to the intervention group and 101 participants to the control group [18, 19]. Since we will pool the data from two sites for the main outcome measures, the total sample size will be equally divided into two study sites.

The sampling strategy for this study involves a multi-stage approach to ensure methodological rigor and reduce potential biases. Initially, eligible villages will be purposefully selected from study areas based on predefined inclusion criteria such as population size, accessibility, and anemia prevalence data, if available. Within each selected village, a household listing will be conducted to identify households with at least one eligible non-pregnant, non-lactating (NPNL) woman of reproductive age. In instances where more than one eligible woman resides in a single household, one participant will be selected using simple random selection methods—such as a coin toss or random number generation—to prevent intra-household clustering and to maintain the independence of observations. This ensures that each household contributes only one participant to the study. Following this, the identified households will be subjected to block randomization, as previously described, to assign participants into intervention and control groups in balanced proportions. This sampling framework enables equitable group allocation, reduces selection bias, and ensures that the study sample is representative of the target population within the selected geographic context.

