### Data collection methods {25}

#### Plans for assessment and collection of outcomes {25a}

Data collection will include both quantitative and qualitative measures to evaluate iron status, dietary intake, adherence, and perceptions of the intervention. Quantitative data will be obtained through structured questionnaires to capture sociodemographic characteristics, health history, and dietary practices, as well as a 24-h dietary recall and Food Frequency Questionnaire (FFQ) to estimate dietary iron intake and food patterns. Laboratory investigations will be carried out at an NABL-accredited laboratory, where trained phlebotomists will collect blood samples for analysis of hemoglobin (Hb), serum ferritin, serum iron, soluble transferrin receptor (sTfR), transferrin saturation (TSAT), total iron binding capacity (TIBC), C-reactive protein (CRP), erythrocyte protoporphyrin, and mean corpuscular volume (MCV). These parameters will be measured at baseline, 6 months, and 12 months, with Hb and ferritin additionally assessed at 3 months. Duplicate testing will be performed on 10% of samples to ensure validity. Qualitative data will be collected through semi-structured interviews and focus group discussions (FGDs) to explore perceptions, facilitators, and barriers to cookware adoption and BCC acceptability, supplemented by field observations recorded during household visits to triangulate adherence and contextual factors. All assessors and laboratory staff will be trained and blinded to group allocation, and standard operating procedures (SOPs) will be followed at all stages to ensure consistency and data quality.

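### The subgroup list in Additional analyses {27d} includes CRP-adjusted versus unadjusted ferritin, which is two versions of the primary outcome in the same women and cannot show effect modification

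*Protocol article*

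**What the plan says.** The protocol article, Additional analyses {27d}, opens: "Pre-specified subgroup analyses will assess effect modification by baseline anaemia status (anaemic vs non-anaemic"). The same sentence completes the list of modifiers with "dietary iron intake categories, and CRP-adjusted vs unadjusted ferritin".

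Table 1 under Outcomes {16} gives the primary outcome as "Serum ferritin (µg/L), CRP-adjusted", analysed as mean change from baseline. Among the exploratory outcomes, the row "Subgroup analysis by baseline anaemia" is the only one for which interaction tests are named. No row defines a subgroup by CRP.

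Inflammation appears in two other places in {27d}: CRP is a model covariate, and "Sensitivity analyses will test the robustness of results to exclusion of participants with elevated CRP". On timing, Plans for assessment and collection of outcomes {25a} says of the laboratory markers, CRP included: "These parameters will be measured at baseline, 6 months, and 12 months".

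**The concern.** A subgroup factor sorts participants into groups, and effect modification asks whether the treatment effect differs between those groups. Baseline anaemia and dietary iron category can do this. Adjusted versus unadjusted ferritin cannot, because both values belong to the same woman at the same visit, and one of them is the primary outcome.

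If the item is carried out and reported under its label, a similar effect on both versions invites the conclusion that the effect does not depend on inflammation. A dissimilar effect invites the opposite conclusion. Neither follows. An arm difference in CRP is a possibility that the protocol itself raises, since the second objective in Objectives {10} makes CRP an outcome. Statistical methods {27a} also relies on the biomarker panel to separate iron deficiency from anaemia of inflammation, so readers will look for a statement about inflammation.

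**Working it through.** **Where the sample size used below comes from.** The plan gives no figure for this item. Its only computed figure is for haemoglobin, with "standard deviation (SD) of 1.2 g/dL and a minimum detectable difference (Δ) of 0.5 g/dL", 80% power and two-sided α of 0.05:

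n = 2 × (1.960 + 0.842)² × 1.2² / 0.5² = 2 × 7.85 × 5.76 ≈ 90.4, so 91 per arm.

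Adding 10% gives 91 × 1.10 = 100.1, so 101 per arm and 202 in total, as stated. (Dividing by 0.90 gives 102 per arm and 204, which is immaterial here.) I use 91 completers per arm.

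**What the contrast measures, log scale.** Let adjusted log ferritin = log ferritin − b × log CRP. For each woman, adjusted minus unadjusted = −b × log CRP. The difference between the treatment effects on the two versions is therefore −b × (arm difference in log CRP). The ferritin effect cancels, whatever its size and whichever women it occurs in. This holds for any b and any CRP distribution.

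**What it measures, µg/L scale.** A correction that multiplies ferritin F by a factor k gives adjusted minus unadjusted = −(1 − k) × F. This moves with F even when CRP is the same in both arms. For example, take k = 0.65 in 30% of women and 1 otherwise, unrelated to F. The mean of (1 − k) is 0.35 × 0.30 = 0.105, so a uniform effect of 1 µg/L produces a contrast of −0.105 µg/L with no effect modification at all.

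**Simulation.** 2,000 trials per scenario, 91 per arm. The documents give none of these inputs, so they are assumptions: 30% with baseline CRP above 5 mg/L, slope 0.25, SD of log CRP 1.1, baseline-to-follow-up CRP correlation 0.6, residual SD of log ferritin 0.5. Entries are the percentage of trials in which the adjusted-versus-unadjusted contrast rejects at 5%.

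| Truth | Log scale | µg/L, regression correction | µg/L, factor 0.65 if CRP > 5 |
|---|---|---|---|
| No effect | 5.6 | 5.1 | 4.7 |
| Uniform effect 0.3 log units | 4.9 | 26.2 | 14.1 |
| Effect 0.5 in non-inflamed only | 4.6 | 19.1 | 9.2 |
| Effect 0.5 in inflamed only | 5.0 | 22.2 | 14.7 |
| No ferritin effect; log CRP lowered by 0.5 | 86.2 | 59.7 | 42.9 |

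The mean log-scale contrast in the last row was 0.124, against 0.25 × 0.5 = 0.125 from the algebra. On the µg/L scale the mean contrast was negative whichever stratum benefited (−2.6 and −3.0 with the regression correction, −1.2 and −1.9 with the factor). Uniform benefit gave the same sign (−3.2 and −1.7). Neither the rejection rate nor the sign identifies modification.

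**Sensitivity to the size of the CRP shift, log scale.** The slope cancels from the test statistic, which is approximately (shift in SDs of log CRP) / √(2/91) = shift / 0.148. Shifts of 0.2, 0.3 and 0.4 SD give 1.35, 2.02 and 2.70, so rejection of about 27%, 53% and 77%. A separate simulation (3,000 trials, slope 0.3) gave 27%, 50% and 77%. If the two versions were stacked as though they came from different women, rejection was 0% when inflammation abolished a 0.5 SD effect.

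**What a real test would offer.** For a group × baseline-CRP interaction with a proportion p raised, the standard error in outcome SDs is √{2 × [1/(91p) + 1/(91(1 − p))]}. Suppose inflammation abolishes a 0.5 SD effect:
- p = 0.15: SE 0.415, ratio 1.20, power Φ(1.20 − 1.96) ≈ 22%
- p = 0.25: SE 0.342, ratio 1.46, power ≈ 31%
- p = 0.35: SE 0.311, ratio 1.61, power ≈ 36%

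Simulation gave 22% to 36% over the same range. In the table's scenarios this interaction had 86% power, but only because 0.5 log units is there a full residual SD (0.5 / 0.5). It rejected in 5% to 6% of trials when there was no modification, including when only CRP shifted.

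**The case against.** The strongest reply is that this is a filing slip. The protocol names no interaction test for this item, and the sensible way to carry it out is to report the treatment effect on each version of ferritin, which is what the fix asks for. Table 1 treats its subgroup analyses as exploratory. Inflammation is already addressed through the adjusted primary outcome, the CRP covariate and the exclusion of women with raised CRP. No objective asks whether inflammation modifies the effect.

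Much of this stands, and it limits the point. The group × version contrast examined above is inferred from the words effect modification; the text does not prescribe it. A reader might also infer that the analysis is simply a test of whether treatment shifts CRP. That is exact only for an additive log-scale correction. The article fixes no correction formula and Table 1 works in µg/L, where the contrast also follows the size of the ferritin effect. Nor do the documents support a claim of very large power loss: such figures need the pots to lower ferritin in inflamed women, which nothing in the protocol suggests.

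What does not stand is that the remedy can be left to the analysis plan. The protocol itself names the factor and calls it pre-specified. An analysis plan could only carry out an uninformative comparison under that label or quietly replace it. The CRP covariate and the exclusion analysis do not test interaction, so they do not supply what the label promises.

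**Conclusion.** The point holds as a misclassification: a comparison of two versions of one outcome is listed as an effect modifier and cannot serve as one on either scale. The log-scale result is algebraic and needs no assumed values. The simulated rejection rates and the 22% to 36% power for a baseline-CRP interaction rest on the stated assumptions about CRP prevalence, slope, correlation and effect size.

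The consequence is confined to an additional analysis. A reader might infer that the primary ferritin comparison or the 202-woman sample size is compromised, or that the protocol is deficient without an inflammation subgroup. Neither follows: the primary comparison does not use this item, the sample size is built on haemoglobin, and a baseline-CRP subgroup is an option, not a requirement. This is a minor correction.

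**What to change.** In Additional analyses {27d}, delete adjusted versus unadjusted ferritin from the subgroup list. Add it to the sensitivity-analysis sentence: the primary ferritin model is re-run with unadjusted ferritin, and the two treatment estimates are shown side by side with 95% CIs and no interaction test.

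If effect modification by inflammation is of interest, name baseline CRP (raised or not, cut-off fixed before unblinding) as a subgroup factor. Test it by a group × baseline-CRP interaction on the primary ferritin outcome, report it with its 95% CI and label it exploratory.

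The cost is a wording change here and in the analysis plan. CRP is already measured at baseline, so no new data are needed. The downside of the optional subgroup is limited power, roughly 20% to 35% if inflammation abolishes a 0.5 SD effect, so a null result there should not be read as evidence of no modification.

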### Statistical methods {27}

#### Primary and secondary outcomes {27a}

Descriptive statistics will be used to summarize baseline characteristics. Continuous variables will be expressed as mean (SD) or median (IQR) as appropriate, and categorical variables as frequencies and percentages. Baseline differences between intervention and control groups will be assessed using independent *t*-tests (or Mann–Whitney *U* tests for non-normal data) and chi-square or Fisher’s exact tests for categorical variables. Standardized mean differences (SMDs) will be calculated, with an SMD < 0.1 indicating adequate baseline balance.

Continuous outcomes such as haemoglobin (Hb), serum ferritin, soluble transferrin receptor (sTfR), and transferrin saturation (TSAT) will be analyzed using linear mixed-effects models with fixed effects for group, time, and group × time interaction, and random effects for participants (and clusters if applicable). Binary outcomes such as anaemia prevalence, adherence, and adverse events will be analyzed using mixed-effects logistic regression. Risk ratios, odds ratios, mean differences, and 95% confidence intervals will be reported. The significance level will be set at *p* < 0.05 (two-tailed). Analyses will be performed using R software.

To provide a comprehensive evaluation of iron status, additional biomarkers will be assessed, including total iron-binding capacity (TIBC), erythrocyte protoporphyrin, mean corpuscular volume (MCV), and C-reactive protein (CRP). These indicators will enable differentiation between iron deficiency, anaemia of inflammation, and other causes of low Hb. Effect size (Cohen’s d) will be calculated for the primary outcomes (Hb and ferritin) to quantify the magnitude of intervention impact**.**

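### Adjusting for fixed baseline covariates as main effects barely changes the group-by-time effect, so it does not address chance baseline imbalance

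*Protocol article*

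**What the plan says.** Three places in the protocol article bear on this.

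- **Primary and secondary outcomes {27a}.** Continuous outcomes are to be analysed with "linear mixed-effects models with fixed effects for group, time, and group × time interaction, and random effects for participants".
- **Outcomes {16}, Table 1.** For ferritin, haemoglobin, soluble transferrin receptor and transferrin saturation the metric is "Mean change from baseline", and the time points are "Baseline, 6 months, 12 months".
- **Additional analyses {27d}.** "Mixed-effects regression models will be applied with adjustment for covariates including age, body mass index (BMI), baseline iron status", and the list goes on with "dietary intake, inflammation (CRP), and socioeconomic status".

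The protocol does not state whether the baseline measurement is an outcome row in the adjusted model, whether covariates enter only as main effects, or whether CRP and diet enter as baseline values. CRP belongs to the laboratory panel of Plans for assessment and collection of outcomes {25a}: "These parameters will be measured at baseline, 6 months, and 12 months, with Hb and ferritin additionally assessed at 3 months". On diet, Outcomes {16} says "Dietary intake and adherence to cookware use will be monitored using structured questionnaires and periodic household visits".

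**The concern.** A group-by-time model with baseline among the visits estimates the treatment effect as a difference between arms in within-woman change. A covariate that is constant within a woman, entered as a main effect, shifts all her visits by the same amount and cancels from that change. Age (in practice), baseline BMI, socioeconomic status and baseline iron status are of this kind.

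The protocol itself treats baseline imbalance as a live issue: {27a} tests baseline differences and takes a standardised mean difference below 0.1 as adequate balance. The adjusted models in {27d} are the only covariate adjustment it describes. If the fixed covariates in them are close to inert, the adjusted result will agree with the unadjusted one however unbalanced those covariates happen to be. A reader would take that agreement as evidence of robustness that was never tested. The precision that the baseline measurement could add would also be lost.

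**Working it through.** **Inputs from the protocol.** SD 1.2 g/dL, difference 0.5 g/dL, 80% power, two-sided 5%, 10% attrition, 202 women in total (Sample size {19}); maximum likelihood under missing at random (Missing data {27c}). **Assumed, not in the protocol:** the correlation r between baseline and follow-up values, the covariate effects and the dropout mechanism.

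**1. The plan's own figure.** n per arm = 2 × (1.960 + 0.842)² × 1.2² / 0.5² = 90.4, so 91. Then 91 × 1.10 = 100.1, rounded up to 101 per arm, which gives the stated 202. (Dividing by 0.90 gives 102 per arm, 204 in total.) I use 91 per arm as the evaluable number.

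**2. Why the fixed covariates cancel.** Write woman i's value at visit t as group, time and group × time terms + γ·xᵢ + uᵢ + error. Her change from baseline is Yᵢₜ − Yᵢ₀. Both γ·xᵢ and the random intercept uᵢ appear in both values and drop out. With complete data the group × time coefficient is the difference in mean change between arms, with or without x.

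**3. Simulation check.** 60 trials per scenario, 202 women, visits at 0, 6 and 12 months, random-intercept REML model. Haemoglobin SD was about 1.15 g/dL and r about 0.60. The dropout scenario lost about 17% by month 12, more than the planned 10%, with dropout depending on baseline haemoglobin. The table gives the 12-month group × time effect (g/dL).

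| Model | Data | Mean estimate | Mean SE | Largest difference from unadjusted in one trial |
|---|---|---|---|---|
| Unadjusted | complete | 0.485 | 0.145 | – |
| Fixed main effects, with baseline Hb | complete | 0.485 | 0.145 | 0.000 |
| Fixed main effects, without baseline Hb | dropout | 0.486 | 0.155 | 0.026 |
| Fixed main effects, with baseline Hb | dropout | 0.485 | 0.150 | 0.054 |
| Fixed main effects + CRP at each visit | complete | 0.482 | 0.143 | 0.067 |
| Fixed main effects + CRP and diet at each visit (diet shifted by the intervention, assumed) | complete | 0.389 | 0.142 | 0.209 |
| Post-baseline visits only, baseline Hb as covariate | complete | 0.484 | 0.129 | 0.184 |

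The unadjusted model with dropout had mean estimate 0.486 and mean SE 0.155. In the two dropout rows the average difference from it was about zero.

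**4. Distance from a truly baseline-adjusted estimate.** Let D₀ and D₁ be the differences between arms at baseline and follow-up. The change contrast is D₁ − D₀. With equal SDs, adjustment for baseline gives D₁ − r·D₀. The gap is (1 − r)·D₀ in size, and SD(D₀) = 1.2 × √(2/91) = 0.178. So:

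- SD of the gap = (1 − r) × 0.178
- SE of the change contrast = 0.178 × √(2(1 − r))
- SE of the baseline-adjusted estimate = 0.178 × √(1 − r²)

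| r | SD of gap (g/dL) | Share of 0.5 g/dL | SE, change | SE, baseline-adjusted |
|---|---|---|---|---|
| 0.3 | 0.125 | 25% | 0.210 | 0.170 |
| 0.5 | 0.089 | 18% | 0.178 | 0.154 |
| 0.7 | 0.053 | 11% | 0.138 | 0.127 |

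**5. How often imbalance arises.** With 101 per arm the SMD of a continuous baseline variable has an SD of about √(2/101) = 0.141 by chance, so about 48% of such variables will exceed the protocol's 0.1 limit.

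**The case against.** - **Baseline as an outcome row is inferred.** This is correct. Table 1 lists measurement times, and {27d} does not say that its model is the {27a} model plus main effects. Naming baseline iron status as a covariate also fits a model with post-baseline outcomes only, where the adjustment would work. Still, a group-by-time model with change from baseline as the metric most naturally includes the baseline row, and a different outcome set for {27d} would have to be stated.
- **Not all listed covariates are fixed.** This stands. A reader might infer that the whole adjusted analysis must return the unadjusted number; the documents do not support that. CRP is measured at 6 and 12 months and diet is monitored during follow-up, and either one entered as measured changes the estimate. It does not rescue the adjustment for baseline imbalance: the movement then comes from variables measured after randomisation, and the behaviour change sessions teach about iron sources, enhancers and inhibitors in the diet, so diet could absorb part of the effect.
- **Exact equality is a special case.** This also stands. It needs complete data and a linear model. With dropout it is approximate, and it does not carry over exactly to the mixed logistic models for binary outcomes.
- **Baseline iron status is undefined.** A reader might infer that one variable stands on both sides of the equation. That follows only if the covariate is the baseline value of the outcome being modelled. Baseline ferritin in a haemoglobin model would not be such a case, though as a main effect it cancels all the same.
- **Such detail belongs in the analysis plan.** Partly fair: a separate plan is announced and not shown. The point is narrower than missing detail. The covariate list in {27d}, read with the model in {27a} and the metric in Table 1, gives an adjustment that does almost nothing for its fixed covariates.
- **The main estimate is unaffected.** True. Change from baseline already subtracts each woman's own starting value, and randomisation leaves both estimators unbiased.

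**Conclusion.** The point holds for the fixed covariates in the linear models. On the natural reading, main-effect adjustment for age, baseline BMI, socioeconomic status and baseline iron status leaves the treatment effect unchanged with complete data, and within about 0.05 g/dL under a simulated dropout heavier than the protocol expects. These covariates do not correct chance imbalance, and agreement with the unadjusted result should not be reported as robustness to it.

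The size is moderate. The gap to a baseline-adjusted estimate has an SD of 0.125 to 0.053 g/dL for r from 0.3 to 0.7, an assumed range. It is chance scatter and lost precision, not systematic bias. The simulated values rest on assumed variances, covariate effects and dropout; the cancellation itself needs only the linear model with baseline as a row. The wording of {27d} should be changed, but the defect does not threaten the main analysis.

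**What to change.** In Additional analyses {27d}, define the adjusted model for continuous outcomes as follows:

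- Outcomes: post-baseline visits only.
- Baseline value of the same outcome as a covariate, with a visit interaction.
- Age, baseline BMI, socioeconomic status, baseline dietary intake and baseline CRP as covariates.
- No adjustment of the treatment effect for diet or CRP measured after randomisation.

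Alternatively, keep baseline as an outcome row, drop baseline iron status from the covariates, and enter the other covariates, at their baseline values, with visit interactions. This addresses imbalance in those covariates, while the outcome's own baseline is still handled by subtraction.

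The cost is a few sentences of wording and a few more model terms, with data already being collected. In the first option, women with no post-baseline value do not contribute. The gain in the simulation was a mean SE of 0.129 instead of 0.145 with complete data.
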